**Methods and design:**

This is a multicenter, randomized, controlled trial that will randomly allocate 234 participants in a 1:1:1 ratio to manual acupuncture group, sham acupuncture group, or western medication group. This trial is primarily designed as an explanatory trial, with the primary comparison being manual acupuncture vs. sham acupuncture to evaluate the specific efficacy of acupuncture; comparisons between acupuncture and western medication are regarded as secondary comparative effectiveness analyses. All groups will receive standard secondary stroke prevention. Manual and sham acupuncture will be administered five times weekly for 3 weeks (30 min/session), while the western medication group will receive oral betahistine mesilate tablets three times daily, 5 days per week, for 3 weeks. Assessments will be conducted at baseline (Week 0), post-treatment (Week 3), and at Week 11. The primary outcome is the Dizziness Handicap Inventory (DHI); secondary outcomes include the Dizziness and Anxiety Rating Scale (DARS), dizziness diaries and adverse event rate during the follow-up period. To test the *a priori* hypothesis that acupuncture improves dizziness by modulating posterior circulation hemodynamics and regional cerebral perfusion in vestibular-related brain regions, cerebral hemodynamics and brain imaging changes will be assessed using transcranial Doppler (TCD), structural magnetic resonance imaging (sMRI), and arterial spin labeling MRI (ASL-MRI) at baseline (Week 0) and post-treatment (Week 3). We specifically hypothesize that acupuncture will increase mean flow velocity (MFV) and reduce resistance index (RI) in the vertebral arteries, basilar artery, and posterior cerebral arteries, enhance regional cerebral perfusion in vestibular-related brain areas, and induce structural changes associated with vestibular compensation.

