**Discussion:**

This study will provide robust evidence on the safety and efficacy of acupuncture for vertigo with PCIS. In addition, it will test a prespecified biological hypothesis that acupuncture may relieve dizziness by improving vertebrobasilar hemodynamics and regional perfusion within vestibular-related brain networks, with corresponding imaging changes associated with clinical improvement. This research aims to offer novel insights into acupuncture as a potential therapeutic approach for vertigo following PCIS.

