### Sample size calculation

As reported in previous studies (8), the mean DHI score for patients treated with betahistine mesilate was 30. For the purpose of sample size estimation, we adopted the clinically meaningful difference derived from our primary comparison: manual acupuncture versus sham acupuncture, assuming a mean DHI score of 21 in the manual acupuncture group, 33 in the sham acupuncture group, with a standard deviation of 20. A 12-point difference in DHI total score between manual acupuncture and sham acupuncture was regarded as clinically meaningful, since the minimal clinically important difference (MCID) for DHI total score has been established as 11 points (26). The trial will include three groups in a 1:1:1 ratio. Using a twotailed test with a category 1 error of 0.05 and a statistical efficacy of 90%, One-Way Analysis of Variance (ANOVA) F-Tests was employed by PASS software (Power Analysis and Sample Size, version 15). The calculations indicate that a minimum of 66 participants per group is required, totaling 198 participants across all groups. Accounting for an estimated drop out rate of 15%, the total sample size should be increased to 234 participants, with at least 78 participants per group.

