### Statistical analysis

Analyses for this study will be conducted in accordance with both the intention-to-treat (ITT) principle and the per-protocol set (PPS) approach. The ITT analysis will include all randomized participants, and the missing data will be imputed using the Last Observation Carried Forward (LOCF) method, with the most recent observed data carried forward for filling. The PPS will include participants who have completed at least 80% of the prescribed treatment. SPSS 23.0 software will be used for statistical analysis. Quantitative indicators are described using mean, standard deviation, median, 25th percentile and 75th percentile. Categorical indicators are described using frequencies and percentages.

To control the Type I error caused by multiple comparisons, the Bonferroni correction will be adopted for pairwise comparisons of the primary outcome (DHI total score) among the three groups (manual acupuncture vs. sham acupuncture, manual acupuncture vs. western medication, sham acupuncture vs. western medication), with the adjusted significance level set at *p* < 0.017 (0.05/3); for secondary outcomes (DARS scores, dizziness diary indicators including attack frequency, duration and severity), the false discovery rate (FDR) method will be used for multiple comparison correction to balance the Type I and Type II error rates in exploratory analysis of multiple secondary indicators.

Since this study is a multicenter clinical trial, sub-center and corresponding baseline values were incorporated as covariates in the generalized linear model for analysis. Additionally, binary logistic regression was employed to analyze the impact of high versus low expectations on the primary efficacy endpoint across groups. The dependent variable in this analysis was response status, defined as participants showing at least a 50% reduction in total DHI scale score from baseline after 3 weeks of treatment (referred to as responders). The independent variable was the level of expectation (high or low).

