Neuroimaging data (sMRI and ASL-MRI) will be analyzed with professional software and standardized methods, and all analyses will be completed by an experienced radiologist who is blinded to the participant group allocation. sMRI data will be preprocessed and analyzed using SPM12 (Statistical Parametric Mapping 12) and FSL (FMRIB Software Library); the preprocessing steps include skull stripping, spatial normalization, tissue segmentation (gray matter, white matter, cerebrospinal fluid) and 8 mm Gaussian kernel smoothing, and then voxel-based morphometry (VBM) and voxel-mirrored homotopic connectivity (VMHC) will be used to analyze group differences in gray matter volume (GMV), cortical thickness and interhemispheric functional connectivity. ASL-MRI data will undergo motion correction, distortion correction and arterial transit time (ATT) correction to calculate cerebral blood flow (CBF) maps; region of interest (ROI) analysis will be performed on vestibular-related brain regions (vestibular nuclei, brainstem, cerebellum, posterior cerebral cortex) to compare group differences in regional CBF, and whole-brain voxel-wise analysis will be conducted to explore potential brain regions with altered perfusion associated with vertigo improvement.

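### The multiplicity rule does not name the TCD and ASL-MRI measures, although they are presented as the test of an a priori hypothesis with no key measure or success rule

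*Protocol article*

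**What the plan says.** The Statistical analysis section of the protocol article sets a two-part rule for type I error. The three pairwise DHI comparisons are Bonferroni-adjusted to 0.05/3, given as 0.017. Then: "for secondary outcomes (DARS scores, dizziness diary indicators including attack frequency, duration and severity), the false discovery rate (FDR) method will be used". The reason given for FDR is that several secondary indicators are being analysed in an exploratory way.

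The mechanistic measures are described elsewhere:

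- The abstract (Methods and design) calls the hypothesis a priori and gives directions: "acupuncture will increase mean flow velocity (MFV) and reduce resistance index (RI) in the vertebral arteries, basilar artery" and the posterior cerebral arteries, together with higher perfusion in vestibular regions and structural change.
- The abstract (Discussion) says of the trial that "it will test a prespecified biological hypothesis that acupuncture may relieve dizziness by improving vertebrobasilar hemodynamics".
- The end of the Introduction makes this the third named objective.
- Table 1 puts TCD, sMRI and ASL-MRI in a row of their own, apart from the secondary outcomes. The abstract's list of secondary outcomes does not include them.
- The neuroimaging part of Statistical analysis specifies group comparisons of regional CBF in four named regions, and adds that "whole-brain voxel-wise analysis will be conducted to explore potential brain regions with altered perfusion associated with vertigo improvement".

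No section names a key mechanistic measure, a correction for this family, or the number of results needed to call the hypothesis supported.

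**The concern.** The plan does not simply leave multiplicity to a later document. It states a rule and names the outcomes the rule covers. Outcomes that it describes as exploratory are corrected, while the family that it describes as prespecified is not mentioned. That is the wrong way round for a family from which the trial intends to draw a conclusion.

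The article's Discussion says the trial leans on objective haemodynamic and imaging markers to reduce its reliance on self-report, and concedes that expectation effects cannot be fully excluded from the self-reported outcomes. A chance finding on one artery or one region could therefore be used to support the DHI result. Without a stated success rule, the choice of which measure represents the hypothesis could be made after the data are seen.

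**Working it through.** **The plan's own figures first.** The inputs come from Sample size calculation: "assuming a mean DHI score of 21 in the manual acupuncture group, 33 in the sham acupuncture group, with a standard deviation of 20"; "the mean DHI score for patients treated with betahistine mesilate was 30"; "The trial will include three groups in a 1:1:1 ratio"; and "Using a twotailed test with a category 1 error of 0.05 and a statistical efficacy of 90" per cent.

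- Grand mean: (21 + 33 + 30)/3 = 28.
- Squared deviations: 49 + 25 + 4 = 78.
- Noncentrality at 66 per group: 66 × 78/20² = 12.87.
- Power of the one-way ANOVA F-test: 90.05%, so 66 per group reproduces.
- Dropout: 66/0.85 = 77.6, rounded up to 78 per group, 234 in total.
- Bonferroni level: 0.05/3 = 0.0167, rounded in the plan to 0.017.

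All of these reproduce, and none depends on the mechanistic measures.

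**Size of the hypothesised family.**

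- TCD: MFV and RI in the vertebral, basilar and posterior cerebral arteries, 2 × 3 = 6. If the vertebral and posterior cerebral arteries are tested per side there are five vessels, 2 × 5 = 10. The TCD section measures them bilaterally but does not say whether sides are tested separately.
- ASL-MRI: four regions (vestibular nuclei, brainstem, cerebellum, posterior cerebral cortex).
- Range: 6 (TCD alone, not split by side), 10 (6 + 4, or TCD alone split by side), 14 (10 + 4).

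Middle and anterior cerebral arteries, sMRI measures, voxel-wise maps and comparisons with the medication arm are left out of the count.

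**Assumptions not in the document.** Each measure is tested at two-sided 0.05, manual versus sham acupuncture only; every null hypothesis is true; any one significant result counts as support; test statistics share a common correlation ρ between 0 and 0.8.

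**Formulas.** For m independent tests, the chance of at least one false positive in either direction is 1 − 0.95^m. In the hypothesised direction only, it is 1 − 0.975^m. For ρ > 0 the same probability is computed for equicorrelated normal statistics, with signs aligned so that the hypothesised direction is positive.

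| m | Either direction: ρ = 0 | ρ = 0.5 | ρ = 0.8 | Hypothesised direction: ρ = 0 | ρ = 0.5 | ρ = 0.8 |
|---|---|---|---|---|---|---|
| 6 | 26.5% | 20.7% | 13.9% | 14.1% | 10.4% | 6.9% |
| 10 | 40.1% | 28.7% | 17.3% | 22.4% | 14.4% | 8.6% |
| 14 | 51.2% | 34.8% | 19.7% | 29.8% | 17.4% | 9.9% |

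The ranges are therefore about 14% to 51% against a nominal 5%, and about 7% to 30% against a nominal 2.5%.

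**The case against.** The strongest reply is that the article is silent, and silence is not a decision to test without correction. Much of this stands.

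- The list in the FDR sentence is visibly incomplete. It omits the quality-of-life impact score, which is the fifth listed secondary outcome, and the adverse event rate, which the abstract calls secondary. Absence from it does not prove exclusion.
- Secondary outcomes announces eight items and lists five. Three are unaccounted for, and there are three objective modalities. They may have been meant to fall under FDR, although Table 1 and the abstract place them elsewhere.
- The hypothesis is worded as a conjunction: MFV up, RI down, perfusion up. If all were required, the error rate would not be inflated. But no section says that all are required.
- The whole-brain analysis is labelled exploratory, and voxel-wise thresholds are commonly left to a fuller document. It should not be held against the a priori claim.

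A reader might infer that the trial will test these measures uncorrected and will probably report a false mechanism. The document does not support that. Larger figures can be produced, such as 73% for ten independent TCD measures over all three pairwise comparisons, or 60% for all 18 independent TCD measures. The first includes sham versus medication, which cannot support an acupuncture mechanism. The second includes middle and anterior cerebral arteries, which the hypothesis does not name.

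What the reply does not remove is that a rule with named scope omits a hypothesis called prespecified, and that this hypothesis has no decision rule.

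**Conclusion.** The point holds as a defect in the scope of the stated rule. The TCD and ASL-MRI measures are presented as a confirmatory test, but the multiplicity rule does not name them and nothing fixes what would count as success.

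Under the any-one-result reading, the false-positive risk exceeds its nominal level in every case in the table: nearly three times nominal at the mild end (13.9% against 5%; 6.9% against 2.5%) and ten to twelve times at the other (51.2% against 5%; 29.8% against 2.5%). These figures rest on the assumed correlation, on testing each measure at 0.05, and on counting any single result as support; the document states none of the three. They do not show that a false positive is likely. The two-sided risk passes 50% only at 14 independent tests.

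The primary DHI conclusion, its Bonferroni rule and the sample size are untouched. The change should be made before the mechanistic data are analysed.

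**What to change.** 1. Extend the FDR rule already chosen to one mechanistic family: MFV and RI in the vertebral, basilar and posterior cerebral arteries plus CBF in the four ASL regions, for manual versus sham acupuncture at Week 3. Say whether sides are averaged or tested separately, because this decides whether the family has 10 or 14 members.
2. State which of these results, or how many, must survive correction for the hypothesis to be called supported. FDR alone does not settle this, since one surviving result could still be read as support.
3. Label the middle and anterior cerebral artery measures, the medication-arm comparisons, the sMRI measures and the whole-brain maps exploratory. Align the structural part of the abstract's hypothesis with that label.
4. Reconcile the eight secondary items announced with the five listed, and say whether TCD, sMRI and ASL-MRI belong among them.

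The cost is a few sentences and no additional participants. The downside is somewhat lower power for each individual TCD or regional CBF measure.

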Pathophysiologically, normal brain function relies on stable metabolic processes, and stroke-induced cerebral metabolic imbalances and secondary structural changes (14). In clinical practice, post-stroke vertigo patients often experience dizziness that is not related to positional changes but rather to prolonged physical activity or sustained attention, associated with cerebral blood flow dysregulation and subsequent oxygen and glucose imbalance (15). Moreover, following ischemic strokes, structural changes in the brain, such as alterations in white matter integrity and gray matter volume, have been well-documented. Studies indicate that structural abnormalities, including infarct location and total lesion volume, may be closely linked to the occurrence of vertigo after stroke (16). In particular, lesions involving the vestibular nuclei, brainstem, cerebellum, or vestibulo-cerebellar structures may be especially relevant to dizziness symptoms (17). Nevertheless, in patients with PCIS, the severity and persistence of dizziness may not be fully explained by lesion topography alone. Residual vertebrobasilar hypoperfusion, altered neurovascular regulation, and secondary reorganization of vestibular-related brain regions may also contribute to symptom burden during recovery (18). Therefore, in the present trial, lesion location will be documented at baseline, while TCD, sMRI, and ASL-MRI will be used as complementary tools to characterize dynamic cerebral hemodynamics, regional perfusion, and structural changes associated with symptom persistence and recovery.

Hence, this study designed as a multicenter, large-sample randomized controlled trial aimed at: (1) Primary objective: To evaluate the specific efficacy and safety of manual acupuncture for PCIS with vertigo or dizziness by comparison with sham acupuncture. (2) Secondary objective: To compare the effectiveness and safety of manual acupuncture with western medication (betahistine) for PCIS with vertigo or dizziness. (3) Mechanistic objective: To test the *a priori* hypothesis that acupuncture alleviates vertigo by improving posterior circulation hemodynamics and regional cerebral perfusion in vestibular-related brain regions. Changes in TCD parameters, ASL-MRI perfusion, and sMRI structural markers will be evaluated and correlated with improvements in DHI scores.

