### Treatment expectations assessment

Before the treatment, participants in each group will be asked, “How do you perceive the final efficacy of the treatment?” Participants will select from one of five options: 1) highly effective (symptom improvement >75%); 2) moderately effective (symptom improvement 50%–75%); 3) slightly effective (symptom improvement 25%–50%); 4) no change (symptom improvement 0–25%). Responses indicating “highly effective” will be categorized as high expectations, while all other responses will be categorized as low expectations.

To minimize expectation bias, outcome assessors and statisticians will remain fully blinded to group allocation throughout the study. In addition, treatment expectation level will be incorporated as a covariate in the statistical analysis of the primary outcome (DHI) to adjust for its potential confounding influence on subjective symptom reports. To further ensure objectivity, all assessments will be performed using standardized procedures, and expectation evaluation will be conducted by a researcher blinded to treatment assignment.

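### Optional improvement: baseline lesion site is recorded but is not among the covariates named for the DHI analysis; adding it could gain a little precision

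*Protocol article*

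**What the plan says.** The covariates for the DHI analysis are named in two places in the protocol article. The Statistical analysis section states that "sub-center and corresponding baseline values were incorporated as covariates in the generalized linear model for analysis". The Treatment expectations assessment section states that "treatment expectation level will be incorporated as a covariate in the statistical analysis of the primary outcome (DHI". Read together, they name three covariates: centre, baseline score and expectation level.

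The Introduction deals with lesions. It says that "structural abnormalities, including infarct location and total lesion volume, may be closely linked to the occurrence of vertigo after stroke", and that "lesions involving the vestibular nuclei, brainstem, cerebellum, or vestibulo-cerebellar structures may be especially relevant to dizziness symptoms". It then limits this: in these patients "the severity and persistence of dizziness may not be fully explained by lesion topography alone". It closes by saying that "lesion location will be documented at baseline", with Doppler and MRI as complementary measures.

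No section uses lesion site in the DHI analysis. The Randomization and blinding section mentions no stratification by it.

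**The concern.** Lesion site is fixed before randomisation, will already be on record, and is put forward by the protocol itself as possibly relevant to symptoms. A baseline factor that predicts the outcome earns its place in a linear model: it takes out residual variance, and it corrects the estimate for whatever imbalance chance has produced. Neither the treatment contrast nor the type I error changes.

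What is at stake is modest: the width of the interval for manual versus sham, and whether a visible imbalance in lesion site can be handled by a rule set in advance. Without such a rule, any adjustment made after the imbalance is seen is open to dispute.

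**Working it through.** **1. The plan's own figure.** The Sample size calculation section works by "assuming a mean DHI score of 21 in the manual acupuncture group, 33 in the sham acupuncture group, with a standard deviation of 20", and takes from earlier work that "the mean DHI score for patients treated with betahistine mesilate was 30". It uses a one-way ANOVA F-test at alpha 0.05 with 90% power.

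- Grand mean: (21 + 33 + 30)/3 = 28.
- Sum of squared deviations: 49 + 25 + 4 = 78.
- Noncentrality at 66 per group: 66 × 78/20² = 12.87, on 2 and 195 degrees of freedom. Power is 0.900; at 65 per group it is 0.896.
- Dropout: 66/0.85 = 77.6, so 78 per group and 234 in total.

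The stated 66, 78 and 234 all reproduce. None of them depends on covariate adjustment.

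**2. Inputs for the covariate question.** From the document: difference 33 − 21 = 12, SD 20, 66 analysed per arm, pairwise level 0.05/3. Assumed, because the document gives neither: the correlation r between baseline and follow-up DHI, and the share R² of the variance left after baseline DHI that lesion site explains. R² is taken as 5–10%.

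**3. Standard error.** The factor is √(1 − R²).

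- R² = 5%: √0.95 = 0.975, a fall of 2.5%.
- R² = 10%: √0.90 = 0.949, a fall of 5.1%.

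This proportional fall does not depend on r.

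**4. Power for manual versus sham.** Residual SD = 20 × √(1 − r²) × √(1 − R²). Noncentrality = 12/(SD × √(2/66)). The test is a two-sided t-test with 130 degrees of freedom and critical value 2.425.

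Baseline DHI is already in the model, so the starting SD must reflect it. At r = 0.5 it is 20 × √0.75 = 17.32.

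| Assumed r | R² = 0 | R² = 5% | R² = 10% | Gain, points |
|---|---|---|---|---|
| 0.3 | 0.881 | 0.898 | 0.915 | 1.7–3.4 |
| 0.5 | 0.938 | 0.950 | 0.960 | 1.2–2.2 |
| 0.6 | 0.969 | 0.976 | 0.982 | 0.7–1.3 |

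If baseline DHI is ignored (r = 0), the same formula gives 0.845 rising to 0.865–0.885, a gain of 2.0–4.0 points. That start does not match the planned model.

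**5. If lesion site explains nothing.** A three-level factor uses 2 degrees of freedom out of about 190, which is negligible.

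**6. Chance imbalance.** Suppose 40% of participants have one lesion type (an assumption). With 78 per arm, the standard error of the difference in proportions is √(0.4 × 0.6 × 2/78) = 0.078. A gap of 10 percentage points or more is 0.10/0.078 ≈ 1.28 standard errors, which happens by chance about 20% of the time.

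**The case against.** The strongest reply is that nothing here is wrong. Randomisation makes manual versus sham valid without lesion site, baseline DHI is already in the model and may carry much of any link between lesion and severity, and no section promises to adjust for lesion site. All of that stands. A statistical analysis plan that is not shown could also add the covariate. Against this, the article does not leave the covariates open: it names three, so the omission can be read as a choice worth a second look.

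The premise is also softer than it may seem. A reader might infer that the protocol treats lesion location as an established predictor of DHI. It does not. The wording is hedged. The link called close concerns whether vertigo occurs, and everyone enrolled has dizziness or vertigo at entry. The Introduction also says that lesion site may not fully explain severity and persistence. What remains is the separate statement that certain sites may be relevant to symptoms. That leaves room for a partial contribution, which is all a covariate needs, but it does not show one.

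A reader might further infer that the DHI analysis adjusts for centre and baseline score alone. The Treatment expectations assessment section rules that out by adding expectation level. The two sections do not give the same covariate list, and they should be reconciled whatever is decided about lesion site.

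Finally, any grouping of lesion sites would be new, since the article defines none. Infarcts at several sites need a coding rule.

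**Conclusion.** The point holds as an optional, low-cost gain in precision. It is not a bias, a contradiction or a threat to the primary comparison. Its size rests on two quantities that the document does not give. With lesion site explaining 5–10% of the variance left after baseline DHI, the standard error falls by 2.5–5.1%. With a baseline correlation of 0.5 as well, power at 0.05/3 and 66 per arm rises by about 1–2 points. A weaker baseline correlation makes the gain in power somewhat larger and a stronger one makes it smaller. If lesion site does not predict DHI, there is no gain and almost no loss.

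The larger gain of 2–4 points, from 0.845, should not be quoted. It applies a share of the remaining variance to the unadjusted SD of 20, as if baseline DHI were not in the model.

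**What to change.** Add baseline lesion site to the primary DHI model as a pre-specified categorical covariate, and list it in one place with centre, baseline DHI and expectation level. Fix the categories and the rule for multi-site infarcts from the baseline record before unblinding. If the team prefers to leave lesion site out, a short reason would settle the point.

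The cost is one sentence in the analysis plan, the coding decisions, and about 2 degrees of freedom for three categories. No further participants or measurements are needed, and the sample size does not change.

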### Participants

#### Inclusion criteria

Participants with dizziness or vertigo meeting the WHO criteria (21) and international Bárány association standards (18) for PCIS will be included. Symptoms may include ataxia, unilateral or bilateral visual, motor or sensory disturbances, double vision, dysarthria or swallowing impairment. Patients must present with TCD or magnetic resonance imaging (MRI) results indicative of vertebrobasilar insufficiency.

Additionally, participants must meet all of the following criteria: 1) in the non-acute stage (defined as >14 days after stroke onset per international stroke guidelines) with stable condition and no acute exacerbation; 2) aged 30 to 80 years, both sexes; 3) dizziness or instability symptoms lasting ≥ 1 week and occurring ≥ 2 times; 4) vertigo attributable solely to central vestibular dysfunction caused by posterior circulation infarction, with no otogenic, ophthalmogenic, or other systemic causes; 5) Basel Scale Index rating scale score of more than 40; 6) able to complete or assist in completing a dizziness diary; 6) willing to cooperate with the study and sign an informed consent form.

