#### Primary outcome

The Dizziness Handicap Inventory (DHI) is the most widely used self-reported measure for assessing dizziness across three domains (25): physical (DHI-P, maximum score of 28), emotional (DHI-E, maximum score of 36), and functional (DHI-F, maximum score of 36). Each item is scored as 0 (no), 2 (sometimes), or 4 (yes). The total score, ranging from 0 to 100, is calculated by summing the scores of all items, with higher scores indicating more severe the dizziness disorder. These outcome measures will be repeatedly assessed at weeks 0, 3, and 11 by a researcher who is blinded to participant allocation.

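### The expectation model uses a purely relative DHI responder rule without adjusting for baseline DHI; adding that covariate is a minor, free improvement to an ancillary analysis

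*Protocol article*

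**What the plan says.** All references are to the protocol article.

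- **Statistical analysis** states the purpose of the model: "binary logistic regression was employed to analyze the impact of high versus low expectations on the primary efficacy endpoint across groups". Responders are "defined as participants showing at least a 50% reduction in total DHI scale score from baseline after 3 weeks of treatment". The rule has no minimum change in points. The section names one independent variable for this model, expectation level (high or low). Sub-centre and baseline values are named as covariates in the sentence before, for the generalized linear model.
- **Inclusion criteria** ask for "dizziness or instability symptoms lasting ≥ 1 week and occurring ≥ 2 times". The only scale score required is "Basel Scale Index rating scale score of more than 40", which is not the DHI. Neither the inclusion nor the exclusion criteria set a minimum DHI.
- **Primary outcome** describes the DHI: "The total score, ranging from 0 to 100, is calculated by summing the scores of all items". Items score 0, 2 or 4, so totals and changes are even numbers.
- **Sample size calculation** says that "the minimal clinically important difference (MCID) for DHI total score has been established as 11 points" and uses this to support a 12-point difference between manual and sham acupuncture.
- **Treatment expectations assessment** grades expectation in bands of percentage improvement. It also enters expectation as a covariate in the primary DHI analysis.

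**The concern.** A 50% fall is a small step from a low starting score and a large one from a high starting score. With no DHI floor at entry and no point floor in the rule, response status partly records where a patient started. At the low end it can be met by a change smaller than the protocol's own MCID. At baseline 0 a percentage fall is undefined.

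This matters for the expectation model because expectation is observed, not randomised. If patients with high expectations tend to be less (or more) severely affected at entry, the regression attributes the baseline effect to expectation. The Introduction presents the quantitative assessment of expectation as one of two new contributions of the trial, so this odds ratio should be free of an avoidable bias.

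**Working it through.** **1. The plan's own figure.** One-way ANOVA with means 21, 33 and 30, SD 20, two-sided alpha 0.05: 66 per group gives power 0.9005. Dropout: 66 / 0.85 = 77.6, rounded up to 78; 3 × 78 = 234. The stated figures reproduce, and none of them uses the responder variable.

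**2. Smallest fall that counts as response.** For an even baseline b this is the smallest even number that is at least b/2. No assumption is needed.

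| Baseline DHI | Smallest qualifying fall | Below 11? |
|---|---|---|
| 4 | 2 | yes |
| 8 | 4 | yes |
| 12 | 6 | yes |
| 16 | 8 | yes |
| 20 | 10 | yes |
| 22 | 12 | no |
| 40 | 20 | no |

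Every nonzero baseline up to 20 can qualify with a fall under the MCID; from 22 upward none can. At 10 or less even complete resolution is a fall of at most 10 points.

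**3. Dependence on baseline.** Suppose the fall is normal with mean 12 (borrowed from the plan's between-group difference) and SD s. Ignoring rounding to even scores, P(response | b) = Φ((12 − b/2)/s).

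| b | s = 15 | s = 20 |
|---|---|---|
| 10 | Φ(0.47) = 0.68 | Φ(0.35) = 0.64 |
| 20 | Φ(0.13) = 0.55 | Φ(0.10) = 0.54 |
| 40 | Φ(−0.53) = 0.30 | Φ(−0.40) = 0.34 |
| 60 | Φ(−1.20) = 0.12 | Φ(−0.90) = 0.18 |

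A simulation used the same mean fall and SDs, baseline SD 20, baseline means 33 to 60, scores rounded to even and limited to 0–100, and baseline 0 excluded. Response occurs in about 60–66% of patients with baseline 2–20 and in 15–34% of those above 20.

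**4. How many patients are affected.** The article gives no baseline mean or SD. With SD 15–20, the share with a nonzero baseline of 20 or less is about 25–27% at mean 30, 10–15% at 40, 3–7% at 50 and 0.5–2.5% at 60. Falls below the MCID as a share of all responders, in the simulation of step 3:

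| Assumed baseline mean | Share of responders with fall < 11 |
|---|---|
| 33 | 17–20% |
| 40 | 11–14% |
| 50 | 5–7% |
| 60 | 2–3% |

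A different model (baseline and Week 3 scores bivariate normal, SD 20, correlation 0.3–0.7, Week 3 mean 21 or 33) gives lower shares: about 5–13% at 40, 2–5% at 50 and about 1% at 60.

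**5. Effect on the expectation odds ratio.** Let expectation have no effect on change in DHI, but let the high-expectation group start 6–9 points lower. The unadjusted odds ratio for response is then 1.24–1.45; with baseline DHI in the model it is about 1.0. Across baseline means 33 to 60, with two equal expectation groups, the unadjusted value spreads somewhat wider (about 1.2 to 1.6). The adjusted value stays near 1.0. If the link ran the other way, the bias would too.

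**The case against.** Four objections carry weight.

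- **The MCID is used for something else.** A reader might infer that the responder rule contradicts the stated MCID. It does not: the 11 points support a between-group difference, and nowhere does the article say that an individual responder must reach them. A 50% fall is a legitimate choice of definition.
- **A percentage rule has a rationale here.** Expectation is itself graded in percentage improvement, and 50% is one of the band limits. An 11-point floor departs from that match and turns complete resolution from 10 to 0 into non-response. It is therefore debatable as the main definition.
- **The reach is small.** A reader might infer that the efficacy conclusion is at risk, or that the role of expectation is judged from this model alone. Neither is supported. Response status is not the primary outcome, not a listed secondary outcome and not in the sample size. Expectation also enters the primary DHI analysis as a covariate, and the Discussion already urges caution about expectancy.
- **The covariate list may be wider than it reads.** The sentence naming baseline values could be meant to cover the logistic model, and a full analysis plan could say so. As printed, however, the article gives that model its own dependent and independent variable, and baseline DHI is not among them.

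What remains is that response depends mechanically on baseline DHI and that the model, as described, does not account for it.

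**Conclusion.** A minor point and a free improvement, confined to the ancillary expectation analysis. Two facts rest on the text alone: the rule is purely relative with no DHI floor at entry, and every nonzero baseline of 20 or less can qualify on a fall under 11 points. The dependence on baseline appears at every mean examined. The number of patients it touches ranges from appreciable at a baseline mean near 33 to very few near 60, and the article does not allow a choice between these. The bias in the odds ratio is conditional: it needs a link between expectation and baseline severity, which is plausible but not documented.

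**What to change.** 1. State that the logistic model of response includes baseline total DHI as a covariate alongside expectation level.
2. State that participants with baseline DHI 0, for whom a percentage fall is undefined, are left out of the responder variable, and report their number.
3. Keep the 50% rule as the main definition. As a sensitivity analysis, repeat the model with response defined as a fall of at least 50% and at least 11 points (12 in practice, since scores are even). Report by arm how many participants have a baseline of 10 or less and so cannot meet it.

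The cost is a few sentences and one extra model run. Baseline DHI is already collected at Week 0 (Table 1), and no procedure or sample size changes. The responder proportion will be lower in the sensitivity analysis, which is why it should not replace the main definition. The wording should be settled before unblinding.
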